### Timetable of work

The planned study duration is 12 months. The main milestones are: months 1 to 2 NHS approvals; months 3 to 9 patient recruitment; months 10 to 11 complete participant follow up at 6 weeks; months 11 to 12 analysis of data, interpretation of results and report writing.

The timetable is described in the Gantt chart in Figure 2.

**Figure 2 F2:**
[figure not shown]
SCARLESS Gannt Chart.

## Endnotes

### Data protection

The trial will comply with the Data Protection Act 1998 [24] and regular checks and monitoring will be in place to ensure compliance. Data will be stored securely in accordance with the Act and archived to a secure data storage facility. The consent form will state that other researchers may wish to access (anonymised) data in the future. CHaRT’s senior IT Manager (in collaboration with the Chief Investigator) will manage access rights to the data set.

### Retention of data

It is intended that data will be retained for at least five years following the end of the study.

### Safety concerns

The SCARLESS trial involves laparoscopic surgical operations for appendicectomy. Possible complications and consequences are:

#### Anaesthesia

All operations carried out under general anaesthesia carry a risk of death, muscle paralysis, technical problems, adverse drug reactions and allergic responses.

#### Abdominal surgery

All abdominal operations carry a risk of death, morbidity, including wound infection, wound hernias, damage to abdominal viscera, bleeding intra and post-operatively, bowel obstruction, respiratory infections, lung collapse, thrombo-embolic complications, complications secondary to existing co-morbidity, for example, ischaemic heart disease and diabetes.

#### Laparoscopic abdominal surgery

Specific complications related to the laparoscopic approach include inadvertent injury to abdominal viscera due to the restricted view associated with laparoscopy, failure to appreciate the extent of pathology, possible sub-optimal repair of intra-operative injuries, inadequate closure of port sites with resulting early and late herniation, which may result in bowel obstruction. With the single port/incision laparoscopic surgery (SPILS) the loss of triangulation of instrumentation, generally considered necessary in laparoscopic surgery, limits surgeon’s access and manoeuvrability.

### Procedure for reporting untoward and related serious adverse events (SAEs)

The UK NHS National Research Ethics Service guidelines for reporting serious adverse events will be followed [25]. For the purpose of SCARLESS, all SAEs, defined as an event resulting from a participant’s appendicectomy treatment that is life threatening, requires prolongation of an existing hospital admission or readmission, results in significant incapacity/disability or is considered to be an important medical event by the clinical team, will be recorded on the Serious Adverse Event Report form. In addition, SAE forms will record all deaths for any cause during the course of the study.

A SAE that is both:

•related (resulted from administration of any of the research procedures) and

•unexpected (that is, the type of event that is not listed as a possible expected complication)

will be notified to the appropriate authorities (Research Ethics Committee (REC) and co-sponsors) within the timelines outlined in the guidelines, as detailed below.

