### Reporting responsibilities of the CI

The Chief Investigator (CI) or deputy will be automatically notified of all SAEs. If, in the opinion of the local surgeon and the CI, the event is confirmed as being related and unexpected, the CI will submit a report to the main REC and the study sponsors within 15 days of the CI becoming aware of it.

As the trial arm to which participants are allocated cannot be blind to the operating surgeons or theatre staff after randomisation has occurred, unblinding is not an issue in this trial. A record of the operative procedures actually carried out will be available in the medical notes if required clinically.

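### Death and catch-all terms appear in the only complication list shown, so under the rule as written a death caused by the trial operation need not be notified to the ethics committee or sponsors

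*Protocol article*

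**What the plan says.** Four parts of the protocol article bear on this.

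- **The notification rule** (Procedure for reporting untoward and related serious adverse events). An SAE goes outside the trial team if it meets two conditions together. It must be "related (resulted from administration of any of the research procedures) and" it must be "unexpected (that is, the type of event that is not listed as a possible expected complication". An event that meets both "will be notified to the appropriate authorities (Research Ethics Committee (REC) and co-sponsors) within the timelines outlined in the guidelines".
- **The CI's duty** (Reporting responsibilities of the CI). The report to the main ethics committee and the sponsors, due within 15 days of the CI becoming aware, again depends on whether "the event is confirmed as being related and unexpected" in the opinion of the local surgeon and the CI.
- **The list** (Safety concerns and its three subsections). It opens with "Possible complications and consequences are". The Anaesthesia subsection says: "All operations carried out under general anaesthesia carry a risk of death, muscle paralysis, technical problems, adverse drug reactions and allergic responses". The Abdominal surgery subsection says: "All abdominal operations carry a risk of death, morbidity, including wound infection, wound hernias, damage to abdominal viscera", and continues with further named complications. The third subsection adds complications of the laparoscopic approach, including visceral injury, unrecognised pathology and herniation.
- **Recording.** Deaths from any cause are entered on SAE forms, and the CI or a deputy is automatically told of all SAEs.

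**The concern.** Expectedness is defined purely by whether a type of event is on a list. Severity, outcome and frequency play no part. Such a definition works only if the list is confined to complications that the ethics committee and sponsors would not need to hear about one by one. The list shown was written as a general description of surgical risk, and it includes the worst possible outcome.

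What is at stake is prompt external notice of a death caused by a trial procedure. The Background states that the safety difference between single-port and conventional laparoscopic surgery is not known. The Laparoscopic abdominal surgery subsection says that the single-port technique gives up instrument triangulation and so limits access. The section on informed consent says that the technique is offered only to patients randomised in the trial. A treatment-related death in this setting is an event that the ethics committee and sponsors would want to receive, and the written rule does not require it to be sent.

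**Working it through.** No calculation applies. The check is to put the rule beside the list and run types of event through it.

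**Step 1: the rule.** Notify if (A) the event is related and (B) its type is not on the list of expected complications. If B fails, neither the reporting procedure nor the CI section requires a report to the ethics committee or sponsors.

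**Step 2: the list.** The reporting procedure does not say where its list is. The only candidate in the article is Safety concerns with its three subsections.

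**Step 3: apply the rule.**

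| Related event | On the list? | Condition B met? | Notification required? |
|---|---|---|---|
| Death | Yes, twice (Anaesthesia; Abdominal surgery) | No | No |
| Visceral injury, bleeding, bowel obstruction, thrombo-embolism, respiratory infection, adverse drug reaction | Yes, each named | No | No |
| Serious technical failure | Covered by technical problems (Anaesthesia) if that term is read broadly | Depends on reading | Depends on reading |
| Intra-abdominal infection | Not named; only wound and respiratory infections are | No if morbidity is a catch-all; yes if it only heads the items after it | Depends on reading |

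The first two rows need no stretched reading. The last two show that the broad terms leave the rule undetermined for some serious events. Intra-abdominal infection is one of the trial's own measures under Clinical outcomes.

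**Step 4: look for another route.** The sentence on deaths requires them to be recorded and does not mention notification. The automatic alert goes to the CI, who must then apply the same two conditions. The article as shown states no separate route to the ethics committee or sponsors for a related death.

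**The case against.** The strongest case on the other side has five parts.

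1. *The two lists may not be the same.* The reporting rule does not cite Safety concerns, which reads as general risk text. A working expectedness list could be in the full protocol or on the SAE form. This stands as a caveat: the link is an inference. But no other list is shown, and if another was meant, the article should say which.
2. *Death may be meant as a consequence, not a complication.* The opening line covers both, and deaths have their own sentence. The reading is possible, but nothing says that death is outside the expectedness test. Both subsections name it in the same run as the complications.
3. *National ethics service guidelines are to be followed.* They might make a related death notifiable. Their text is not available here, and the article goes on to write out its own definition of unexpected. If the two differ, the article needs correcting for that reason.
4. *The surgeon and the CI use judgement.* They do, but the question put to them is whether the event is related and unexpected, and the procedure has already defined unexpected.
5. *Capture is complete.* This stands in full. All deaths and SAEs are recorded and the CI is told of every SAE.

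A reader might go further and infer that almost no event could ever be notified. The documents do not support that. In the Abdominal surgery subsection, morbidity can naturally be read as a heading for the items that follow it, and on that reading serious events such as intra-abdominal infection remain notifiable. A reader might also infer that the trial has no external safety check. That is not shown either: a Trial Steering Committee appears under Abbreviations, and one section between Data protection and Retention of data was not available for this review.

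**Conclusion.** The point holds in a limited form. As written, the rule does not require a death caused by the trial operation to be notified to the ethics committee or sponsors, because the only list shown names death. The same applies to the many serious complications that are individually named, and the broad terms make the position of others unclear. The defect is in onward notification, not in recording or in informing the CI.

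This rests on two assumptions: that the Safety concerns text is the list the rule means, and that the article's own definition of unexpected is what staff would apply. It is a stated rule that works badly when combined with a stated list, not detail that a condensed article may leave out. It does not affect the sample size, the comparison of the groups or the analysis. It should be corrected because it concerns participant safety and the correction is small.

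**What to change.** Reconcile Safety concerns with the reporting procedure by three changes of wording.

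1. In the reporting procedure, state which named complications form the list against which expectedness is judged.
2. Leave death and the catch-all terms morbidity and technical problems out of that list.
3. Add to the reporting procedure that any death judged related is reported to the ethics committee and sponsors within the 15 days already given under Reporting responsibilities of the CI.

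The Anaesthesia, Abdominal surgery and Laparoscopic abdominal surgery subsections can stay as they are, as a description of risk. The cost is a short edit to the safety text and at most a few additional reports. Design, sample size, treatment and data collection do not change.

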### Reporting responsibilities of the CI

The Chief Investigator (CI) or deputy will be automatically notified of all SAEs. If, in the opinion of the local surgeon and the CI, the event is confirmed as being related and unexpected, the CI will submit a report to the main REC and the study sponsors within 15 days of the CI becoming aware of it.

As the trial arm to which participants are allocated cannot be blind to the operating surgeons or theatre staff after randomisation has occurred, unblinding is not an issue in this trial. A record of the operative procedures actually carried out will be available in the medical notes if required clinically.

### Ethical issues and arrangements

The North of Scotland Ethics Committee (NOSRES) reviewed and approved this study on 08 December 2010 (REC reference number: 10/S0802/77).

### Risks and benefits

The benefit to the participants participating in the trial is the chance of receiving a less invasive treatment for their appendicectomy. We believe this study does not pose any specific risks to individual participants beyond those of any laparoscopic surgery, provided sound clinical judgement is exercised to convert to multi-port or conventional surgery when necessary.

### Information about risks and benefits and informed consent

Participants are informed of known risks by means of the Patient Information Sheet. Patients will have surgery whether they are in the study or not and we anticipate no additional risk to those who are randomised. Patients who are ineligible or decline participation in the study will have standard open or three-port laparoscopic surgery as these are the standard types of surgeries undertaken at Aberdeen Royal Infirmary. SPILS will only be available to patients randomised within the trial.

## Abbreviations

ASA: American Society of Anaesthiologists; ARI: Aberdeen Royal Infirmary; BIQ: Body Image Questionnaire; BMI: Body Mass Index; CHaRT: Centre for Healthcare Randomised Trials; CI: Chief Investigator; CSO: Chief Scientist Office; CRF: Case Report Form; GP: General Practitioner; GCP: Good Clinical PracticeHEQ Hospital Experience Questionnaire; ISRCTN: International Standard Randomised Controlled Trial Number; IT: Information Technology; IVR: Interactive Voice Response; mm: Millimetres; MRC: Medical Research Council UK; NHS: National Health Service; NOSRES: The North of Scotland Research Ethics Committee; NRS: Numerical Rating Scale; PMG: Project Management Group; PQ: Participant Questionnaire; PROs: Patient Reported Outcomes; QID: 4 Times a day; REC: Research Ethics Committee; RCT(s): Randomised Controlled Trial(s); SAEs: Serious Adverse Events; SCARLESS: Single Centre Appendicectomy RCT: Laparoscopic vs Endoscopic Single-port Surgery; SPILS: Single Port/Incision Laparoscopic Surgery using either a proprietary device or multiple trocars inserted through a single incision; TSC: Trial Steering Committee; UK: United Kingdom; vs: Versus.
